### IL-6

Central nervous system inflammation significantly contributes to postoperative cognitive dysfunction, and increased expression of inflammatory factors often suggests early cognitive impairment [39]. IL-6 is a cytokine with a wide range of biological activities and is essentially a glycoprotein consisting of 184 amino acids that play an essential role in the inflammatory response of the body. The cells that synthesize IL-6 in the brain are astrocytes, microglia, and endothelial cells, and the cells that synthesize IL-6 in the periphery are mononuclear macrophages and lymphocytes [14]. Serum IL-6 levels are also correspondingly elevated after brain injury, which may be related to the increased early or ultra-early synthesis of IL-6 in the brain, disruption of the blood–brain barrier, and increased intestinal permeability to bacterial toxins. Weaver et al. [15] performed a rigorous regression analysis and found that elevated plasma levels of IL-6 are closely related to cognitive impairment and are a risk factor for cognitive impairment. Using transgenic mice overexpressing IL-6, the authors found that IL-6 plays a causal role in neuropathophysiological aspects such as reduced memory and learning abilities. This result further confirms that detecting IL-6 levels in plasma contributes to the early detection of cognitive impairment.

In summary, changes in the levels of both IL-6 and NSE may be used as markers of brain injury, and NSE has high sensitivity and specificity. In addition, recent evidence from animal experiments and clinical studies also supports the possibility of a close association between the levels of these two proteins and early postoperative cognitive dysfunction, which can be used as early warning indicators of postoperative cognitive dysfunction. Therefore, these two markers will be selected in this study to assist in assessing the extent of brain injury and to explore the potential cerebral protective role of PHC and the possible mechanisms by which PHC improves early postoperative cognitive function outcomes.

### Standardized perioperative care

#### Anesthesia induction

Through the standardized preoperative visit and corresponding optimal preoperative preparation, the patient will meet the requirements for elective surgery and fasting time, will not be administered any anticholinergic drugs or anti-5-hydroxytryptamines for 30 min before surgery, and will then be transported to the operating room. After admission, invasive arterial blood pressure (IABP), electrocardiogram (ECG), heart rate (HR), partial pressure of end-expiratory carbon dioxide (PETCO_2_), body temperature (T), pulse oximetry (SpO_2_), and electroencephalographic bispectral index (BIS) will be routinely monitored with a multifunctional anesthesia monitor connected to a brain tissue oxygen saturation (rSO_2_) monitor, and peripheral venous access will be opened. Atropine at 0.3–0.5 mg, sufentanil at 0.2–0.4 μg/kg, propofol at 1.5–2.0 mg/kg will be injected intravenously, and rocuronium at 0.6–0.9 mg/kg will be injected intravenously when the BIS value decreases to 45–55. After reaching the inotropic time, tracheal intubation will be performed, and mechanical ventilation will be connected to the anesthesia machine after confirming that it is placed in the trachea. After anesthesia, a retrograde puncture tube will be placed through the right internal jugular vein to the bulb of the internal jugular vein, and the tube will be sealed with heparin for blood sampling (the rate of blood collection from the bulb of the jugular vein is < 2 mL/min). A radial artery puncture tube will be placed to collect arterial blood samples.

#### Anesthesia maintenance

The MAC value was maintained between 1.1–1.3 by inhalation of 1.5%-2.0% sevoflurane and 60% N_2_O, the BIS value was held between 40–60, and remifentanil was continuously pumped at a starting rate of 0.01 µg/kg/ min. The pump speed of remifentanil was adjusted according to the fluctuation of intraoperative blood pressure (the maximum dose was not more than 1ug/kg/min), and the anesthesiologist added sufentanil at a quantity of 5 µg each time according to the fluctuation of the patient's hemodynamics. The inhalation of sevoflurane, N_2_O, and remifentanil will be stopped when the skin is sutured. After the patient's consciousness was clear, muscle strength and throat reflex recovered, the endotracheal tube was removed by adequate sputum suction, and the patient was sent to the Post Anesthesia Care Unit (PACU). The use of any awaking drug was prohibited if it was not necessary during the recovery period after surgery. Notably, the intraoperative depth of anesthesia should be maintained as stable as possible because the relationship between the depth of anesthesia and postoperative cognitive function outcome is highly controversial. The results of previous clinical studies and meta-analyses are contradictory, with some studies suggesting that a shallower depth of anesthesia is more favorable for improved postoperative cognitive function outcomes [65, 66], some confirming that a deeper level of anesthesia is associated with better cognitive function, especially the ability to process information, 4–6 weeks after surgery [67], and some findings even showing no significant correlation between depth of anesthesia and postoperative cognitive function [68]. Therefore, we should exclude the effect of the anesthesia depth on the study as much as possible. After tracheal intubation, the respiratory rate and tidal volume will be adjusted, and PaCO_2_ will be maintained within the respective target values in both groups.

#### PACU and ward

After the operation, the patient will be returned to the PACU for observation of awakening. After transfer to the PACU, the anesthesia nurse will connect the patient-controlled intravenous analgesia (PCIA) device and the drug formulation as follows: 2 µg/kg sufentanil and 0.3 mg of ramosetron, diluted to 100 ml using saline). Parameters are set as follows: a single compression dose of 2 ml/time, lock time of 15 min, and maximum dose of 8 ml per hour. The anesthesia nurse will assess the patient's pain score using the NRS method. When the patient's NRS score is ≥ 4 at rest, the PCIA analgesic device is pressed, and if the NRS score is ≥ 4 after the first press for 10 min, 5 µg of sufentanil will be administered intravenously as remedial analgesia until the pain score is < 4. When the patient is fully conscious, and the limbs can perform intended activities, the patient will be given air inhalation for observation for 1–2 min, and if the oxygen saturation is maintained above 95%, the patient will be transferred out of the PACU. On a postoperative day, nurses will assess pain scores in the surgical ward using the same NRS for all patients. All patients will receive 50 mg of flurbiprofen ester administered at 24 h intervals. The ward nurses are unaware of the grouping of patients and their interventions. Preoperative admission instruction will be put into practice: patients and family members assess pain scores themselves postoperatively, and again, the PCIA analgesia device is pressed when the NRS score is ≥ 4. If the NRS score is ≥ 4 after the first press for 10 min, 5 µg of sufentanil will be administered intravenously as remedial analgesia until the pain score is < 4.

### Sample size calculations

According to data previously reported by our institution, rSO_2_ values at wakefulness range from 60 to 80% for elderly patients with NFBF, consistent with previous studies [69]. Although the earlier studies of cerebral oxygen monitoring did not address the point of "NFBF," we obtained the same rSO_2_ interval in the preoperative awake state, which does not mean that this discussion is meaningless. However, the natural state of elderly patients with NFBF may not be significantly different from the average population due to the body's compensation, but when entering the general anesthesia and surgery state, the lack of cerebrovascular self-regulatory reserve capacity and the regional cerebral microcirculatory disorders of these patients only become apparent with the intensification of the systemic stress response and the increase of hemodynamic fluctuations.

Interestingly, a "15%" change in rSO_2_ values at the end of surgery relative to baseline values in both groups is considered clinically significant [70]. However, we need to state that "15%" is a research inference made for the anti-Trendelenburg position, and the laparoscopic colorectal surgery in this study was the Trendelenburg position. Due to the apparent position difference, we cannot ignore the secondary changes in cerebral perfusion and CBF. Continuing to choose the "15%" cutoff may overestimate the effect on the intervention group. Therefore, we used the more conservative "10%" relative change as the clinically significant margin in our trial. A baseline rSO_2_ of 60% to 80% was used, and the absolute change in rSO_2_ from baseline to the end of surgery was assumed to be 0% in the control group according to the pilot study and 8% in the intervention group (a 10% increase from baseline rSO_2_ of 80%). The sample-size calculation for the test of difference was performed with the use of PASS 15.0.5 software, and the total sample size needed for an unpaired t-test was calculated to be 68 at a two-sided significance level of 5% and 90% power. Considering the loss of a follow-up rate of 10%, our final sample size will be 76 (evenly distributed between the two groups).

### Statistical analysis

Data will be analyzed using Statistical Package for Social Science 25.0 software. The Shapiro–Wilk test is used to test the normality of continuous variables, expressed as means and SDs if they are normally distributed and as medians and interquartile ranges if they are non-normally distributed. Baseline, Intraoperative, and postoperative indicators between the intervention and control groups are analyzed by t-tests, Mann–Whitney U test, chi-square test, continuous corrected chi-square test, or Fisher's exact test (Table 3). All primary and secondary outcomes analysis will be based on intention-to-treat (ITT) which means all patients who accept randomization will be included in the final statistical analysis, regardless of whether they received the intended intervention. We will also conduct per-protocol (PP) analysis for primary and secondary outcomes. ITT analysis usually attenuates differences between two groups, and PP analysis exaggerates differences between two groups. We will explore the consistency of ITT and PP analysis results and verify the results' reliability if they are consistent in the end. For the primary outcome, linear regression models will be used to generate unadjusted effect sizes with 95% confidence intervals. Preoperative baseline and intraoperative data are also included in the linear model to generate adjusted effect sizes and 95% confidence intervals. The analysis of repeated measures (rSO_2_, Da-jvO_2_, CERO_2_) will be performed using generalized estimating equations (GEE), with patient code (ID) as the within-subject variable, time as the between-subject variable, and rSO_2_, Da-jvO_2_, and CERO_2_ as the dependent variable. The ACE-R scores of the intervention and control groups will also be analyzed by GEE. What we need to be clear is that we will not adjust for multiple comparisons of secondary outcomes at numerous measurement time points, and we will focus on the separate effects of intervention because these results are exploratory. The incidence of CDE and DNR between the intervention and control group will be analyzed by the chi-square test, continuous corrected chi-square test, or Fisher's exact test. The serum NSE and IL-6 concentrations between the intervention and control groups are analyzed by covariance (ANCOVA) analysis, and the least-squares mean (LSM) difference and 95% CI will be estimated. Postoperative adverse events will be analyzed using the safety analysis set, which refers to patients who received at least one intervention in their group. Postoperative adverse events are categorical data, and the chi-square test, continuous corrected chi-square test, or Fisher's exact test will be used for statistical analysis.

**Table 3 Tab3:** Baseline and intraoperative characteristics to be compared between the two groups

Baseline Characteristics	Intraoperative characteristics
**Age** (year)	**Anesthesia time** (min)
**Sex**	**Operation time** (min)
• Male	**Pneumoperitoneum time** (min)
• Female	**Surgical method**
**Weight** (kg)	**Intraoperative hypotensive events**
**BMI** (kg/m^2^)	**Bradycardia events**
**ASA** physical status	**Blood transfusion events**
• I	**Blood loss** (ml)
• II	**Infusion quantity** (ml)
• III	**Vasoactive drug use** (ug)
**rSO**_**2**_ (%)	• Ephedrine
**PaO**_**2**_ (mmHg)	• Phenylephrine
**PaCO**_**2**_ (mmHg)	• Norepinephrine
**Hb** (g/L)	• Epinephrine
**Ejection fraction** (%)	**Opioid consumption** (ug)
**Stroke volume** (ml)	• Remifentanil
**Comorbidity**	• Sufentanil
• Hypertension (I/II/III)	• Tramadol
• Diabetes	• Oxycodone
• COPD	**Blood gas analysis of different period (T**_**1**_**/T**_**2**_**/T**_**3**_**/T**_**4**_**)**

Blood gas analysis: pH/ PaCO_2_/ PaO_2_/ Hb/ Lac/ Glu

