### Operating method

In this study, we will use a FORE-SIGHT regional oximeter (CAS Medical Systems, Inc.) to collect rSO_2_. This regional oximeter monitors intracerebral rSO_2_ using NIRS and reflectance oximetry, displaying absolute rSO_2_ values and trends. Absolute oximetry values will be defined as rSO_2_ measured with an oximetry probe calibrated with a fixed arterial-to-venous blood ratio. In our study, only absolute oximetry data will be extracted and analyzed. We will install NIRS sensors on each side of the patient's forehead and measure rSO_2_ in both brain hemispheres. Baseline rSO_2_ will be recorded before the start of any medication and before induction of anesthesia, and subsequent rSO_2_ measurements will be recorded every 10 s until the last surgical suture is complete. At the end of the procedure, the data for the entire test cycle will be read via a memory stick through the USB port on the instrument. Moreover, the data collected (within the first two hours of surgery) will finally be presented as a line graph with data visualization software (GraphPad Prism) to visualize the temporal trend of changes in rSO_2_ in both hemispheres. Although we will perform dynamic acquisition of rSO_2_ values throughout the procedure for each patient, the visualization will be limited to 2 h after the start of the procedure due to the substantial variation in the time of the procedure between patients. The absolute change in percent change in rSO_2_ will be calculated by subtracting the baseline rSO_2_ value (T_0_) from the value measured at the end of the procedure (T_4_), multiplied by 100%. The investigators will collect rSO_2_ data from the sensors placed on the patient's left and right forehead.

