The relationship between PaCO_2_ and CBF has been well documented in recent years, both in terms of underlying physiological mechanisms and in clinical practice, but the relationship between PaCO_2_ and rSO_2_ has not been clarified. Many factors affect rSO_2_, such as cardiac output, volume per beat, MAP, Hb affinity for oxygen, cerebral vascular self-regulation, and surgical position adjustment. Among them, PaCO_2_ may exert a direct and significant effect on the affinity of hemoglobin for oxygen by regulating pH and subsequently through the Bohr effect. Throughout the procedure, we can control for potential confounders such as PaCO_2_, pH, MAP, and intraoperative body position. We will make preoperative baseline adjustments to the subject's MAP, Hb level, and cardiac output. However, intraoperative changes in cardiac output, the brain's self-regulatory effect on the arteriovenous blood volume ratio, the effect of laparoscopic surgery on thoracic pressure, and the subsequent effects on cardiac output, volume per beat and systemic vascular resistance cannot be measured objectively and realistically.

In conclusion, although an increasing number of studies have explored the relationship between PaCO_2_/PHC and rSO_2_ in recent years, the current research evidence only provides an objective description of the clinical phenomenon, as shown in the Table 4. The specific underlying mechanism of action remains unclear, and we should not draw hasty conclusions.

**Table 4 Tab4:** Summary of related studies on the relationship between mild hypercapnia and rSO_2_

**Author**	**Year**	**Subjects**	**Trial**	**Outcomes** (Mild hypercapnia)
Eastwood et al. [78]	2016	Cardiac arrest	Prospective double crossover physiological study	Increases cerebral oxygenation
Akca et al. [79]	2002	Abdominal or orthopaedic surgery	RCT	Improves tissue oxygenation; Increase cerebral oxygen saturation; Reduce the incidence of wound infection
Murphy et al. [27]	2014	Shoulder surgery	RCT	Higher intraoperative rSO_2;_ Lower incidence of CDE
Park et al. [80]	2021	Gynecological Laparoscopic surgery	RCT	Increases rSO_2_
Wong et al. [71]	2020	Elective major surgery	RCT	Associated with a stable increase in rSO_2_

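### Two primary-outcome regressions are planned without saying which decides, and neither is a clean adjustment for the baseline rSO2 recorded in every patient

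*Protocol article*

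**What the plan says.** All references are to the protocol article.

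- **Primary variable.** Operating method defines it as "calculated by subtracting the baseline rSO_2_ value (T_0_) from the value measured at the end of the procedure (T_4_), multiplied by 100" percent, that is, the T4 minus T0 difference in rSO2. T0 is recorded before any drug is given.
- **Sizing.** Sample size calculations assumes a change "assumed to be 0% in the control group according to the pilot study and 8% in the intervention group", and "the total sample size needed for an unpaired t-test was calculated to be 68 at a two-sided significance level of 5% and 90% power". Allowing for 10% loss gives 76. No SD of change is stated; on spread the section says only "A baseline rSO_2_ of 60% to 80% was used".
- **Primary estimates.** Statistical analysis first says "For the primary outcome, linear regression models will be used to generate unadjusted effect sizes with 95% confidence intervals". The sentence after it plans a further estimate from a linear model that also contains preoperative baseline and intraoperative data. The covariates are not listed, and neither estimate is designated as the one that decides.
- **Candidate covariates.** Table 3 lists rSO2 among the baseline characteristics. Its intraoperative column includes blood gases at T1 to T4, with pH and PaCO2 among them, as well as hypotensive events and vasoactive drug use. The Discussion says "We will make preoperative baseline adjustments to the subject's MAP, Hb level, and cardiac output"; rSO2 is not in that sentence.
- **Secondary markers.** In the same Statistical analysis paragraph, "The serum NSE and IL-6 concentrations between the intervention and control groups are analyzed by covariance (ANCOVA) analysis".

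**The concern.** Two estimates of one primary effect, with no order between them, leave open which result the trial stands on. Neither is the one a trial with a measured baseline would normally choose.

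Subtracting T0 does not adjust for it. A change score fixes the baseline slope at 1, whereas a model with T0 as covariate estimates the slope. When the true slope is not 1, part of any chance T0 difference between arms passes into the unadjusted estimate, and the interval is wider than the data require.

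The second model has the opposite fault. Study design and the section on PaCO2 measurement show that ventilation is adjusted to reach a different PaCO2 range in each arm. Intraoperative PaCO2 and pH are therefore consequences of allocation. With them in the model, the group coefficient no longer estimates the whole effect of the assigned ventilation on rSO2, only what is left after the route through PaCO2 is held fixed.

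**Working it through.** **1. The plan's own figure.** Inputs: difference 8 points, two-sided 5%, 90% power, 34 per arm. The SD is missing, so 68 cannot be reproduced from the stated inputs alone. Solving the t-test backwards, 34 per arm needs an SD of change between 9.87 and 10.03. With SD 10, power is 90.2%. Loss: 68/0.90 = 75.6, rounded up to 76, which agrees.

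**2. Formula for the gain.** Let b be the T0 SD, s the T4 SD, ρ their correlation, β = ρs/b the baseline slope and D the SD of change.

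- Var(change) = D² = s² + b² − 2ρbs
- Var(adjusted) = s²(1 − ρ²)
- Proportional variance gain = (β − 1)²b²/D²
- Shift in the unadjusted estimate per unit of T0 imbalance = β − 1

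With s = b, the gain reduces to 1 − (1 + ρ)/2.

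**3. Case A: equal SDs, D = 10 (assumption).** Here b = 10/√(2(1 − ρ)).

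| ρ | implied b | variance gain | SE reduction | power at 8 points, 34 per arm |
|---|---|---|---|---|
| 0.3 | 8.5 | 35% | 19.4% | 98.1% |
| 0.5 | 10.0 | 25% | 13.4% | 96.3% |
| 0.7 | 12.9 | 15% | 7.8% | 94.1% |
| 0.9 | 22.4 | 5% | 2.5% | 91.5% |

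A simulation of 20,000 trials at ρ = 0.5 gave a variance ratio of 0.757, against 0.75 from the formula. A one-SE T0 imbalance at ρ = 0.5 is 10 × √(2/34) = 2.43 points. It shifts the unadjusted estimate by (0.5 − 1) × 2.43 = −1.2 points: an arm that starts low appears to rise more.

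**4. Case B: baseline SD 5 to 6, D = 10 (assumption).** Values confined to 60-80% cannot have an SD above 10, and reach 10 only if half sit at each end. A 20-point range suggests roughly 20/4 = 5, or 20/√12 = 5.8 if uniform. Solving D² = s² + b² − 2ρbs for s:

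| ρ | b | s | β | variance gain |
|---|---|---|---|---|
| 0.5 | 5 | 11.5 | 1.15 | 0.6% |
| 0.5 | 6 | 11.5 | 0.96 | 0.1% |
| 0.7 | 5 | 12.8 | 1.80 | 15.9% |
| 0.7 | 6 | 13.2 | 1.54 | 10.7% |

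With b = 5, a one-SE imbalance is 5 × √(2/34) = 1.21 points. The shift is 0.15 × 1.21 = 0.2 points at ρ = 0.5 and 0.80 × 1.21 = 1.0 point at ρ = 0.7. Both have the opposite sign to case A: the arm that starts low appears to rise less. Case B also requires the T4 SD to be about twice the T0 SD, which the article neither states nor rules out.

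**5. The adjusted model.** The size of the distortion from conditioning on PaCO2 and pH cannot be computed from the article. Its source is clear: the arms are held to PaCO2 35-45 and 45-55 mmHg, so group and intraoperative PaCO2 are nearly the same variable by design.

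**The case against.** A reader might infer that the primary effect simply is unadjusted and that the trial throws away a quarter of its precision. The documents do not support that, for three reasons.

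- The sentence following the unadjusted estimate plans an adjusted one. Table 3 counts rSO2 as a baseline characteristic, so T0 rSO2 may well be among its covariates. The Discussion sentence on MAP, Hb and cardiac output concerns physiological confounders and is not a covariate list that excludes rSO2.
- The 25% is a reduction in variance; the interval narrows by about 13%. It also needs ρ = 0.5 and a baseline SD near 10, which fits poorly with a 60-80% range. On a baseline SD of 5 to 6 with the same SD of change, the gain at ρ = 0.5 vanishes, and the direction in which a baseline imbalance pushes the estimate is not fixed. If instead the SDs are equal and the baseline SD is 5 to 5.8, the unadjusted test already has over 99.7% power at 8 points for ρ from 0.3 to 0.7, so there is little power to gain.
- The unadjusted comparison is not an error. It is unbiased over randomisations, keeps its type I error and is the test the sample size was computed for. Using ANCOVA for NSE and IL-6 is no contradiction.

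It is also fair to say that a full covariate list belongs in an analysis plan that is not shown. That answers the missing list. It does not answer what the article does state: two primary-outcome models, unranked, one of which is expressly to include intraoperative data.

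**Conclusion.** The point holds in a limited form. As written, the primary outcome has two competing estimates. The only one free of post-randomisation covariates makes no use of T0 rSO2 beyond subtracting it, and the only one that uses baseline data can absorb part of the treatment effect.

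The benefit of a clean baseline adjustment is real in principle but uncertain in size: from about 0% to 35% of the variance over the correlations of 0.3 to 0.9 and the baseline SDs tabulated above. Every one of those figures rests on an assumed correlation and assumed SDs. Beyond one degree of freedom, the adjustment is not expected to lose precision under any of them. This is an inexpensive improvement in precision and clarity, and it does not make the planned test invalid.

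**What to change.** In Statistical analysis, replace the two sentences on the primary outcome with one designated primary analysis: a linear model of the T4 minus T0 change in rSO2 (or, equivalently for the group effect, the T4 value) on group, with T0 rSO2 as the prespecified covariate, reported as the group difference with its 95% confidence interval and p-value. Keep the unadjusted difference as a supportive estimate. Keep intraoperative variables out of the primary model, and label any model that contains them exploratory.

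The cost is one or two sentences of text and one degree of freedom. No new data are needed because T0 rSO2 is already recorded, and the sample size of 76 stands. The change should be made before the outcome data are analysed and the allocation is decoded.

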## Methods

### Study design, setting and participants

Between October 2022 and July 2023, we plan to conduct an RCT at Shengjing Hospital of China Medical University (Shenyang, China), a university teaching, higher education, large general hospital. The trial period is expected to be 10 months, during which patient recruitment, intervention implementation, and postoperative follow-up will be conducted in an orderly manner according to the actual situation. The final results are expected to be reported in October 2023. Participants will be screened from the patients proposed for elective laparoscopic colorectal surgery in the gastrointestinal surgery department of the hospital. Patients who are eligible for elective major surgery are identified after a preoperative evaluation and receipt of written informed consent before the patient's surgery date. Patients who meet the screening criteria will be randomly assigned 1:1 to the control group (Conventional ventilation group parameters: Tidal volume10 ~ 12 mL/kg, Respiratory rate 14 ~ 16 bpm, Suction/Respiration ratio 1:2, PaCO_2_ 35 ~ 45 mmHg, PEEP 0 cmH_2_O, FiO_2_ 40%) and the intervention group (Permissive hypercapnia group parameters: Tidal volume 6 ~ 8 mL/kg, Respiratory rate 12 ~ 14 bpm, Suction/Respiration ratio 1:2, PaCO_2_ 45 ~ 55 mmHg, pH > . 7.2, PEEP 0 cmH_2_O, FiO_2_ 40%), and 38 patients will be included in each group. Baseline preoperative rSO_2_ values will be recorded, and real-time intraoperative rSO_2_ monitoring will be performed by investigators who are not providing the clinical intervention. In addition, patients will be followed up postoperatively with MMSE scale to assess early postoperative cognitive function. The patients with postoperative MMSE scores ≤ 23 and a decrease of more than 2 points from the baseline value were defined as delayed neurocognitive recovery (DNR). It should be noted that the follow-up personnel have received standardized training in advance, to ensure that the survey scale can be used scientifically and correctly (Fig. 1).

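### The adjusted model for the primary outcome admits intraoperative (post-randomisation) data without restriction, so its estimate need not be the effect of allocation, and the plan does not rank it against the unadjusted one

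*Protocol article*

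**What the plan says.** The Statistical analysis section of the protocol article plans two regression estimates for the primary outcome, the change in rSO2 from T0 to T4. The first is unadjusted: "For the primary outcome, linear regression models will be used to generate unadjusted effect sizes with 95% confidence intervals". The second is adjusted: "Preoperative baseline and intraoperative data are also included in the linear model to generate adjusted effect sizes and 95% confidence intervals". The second sentence names no covariates and excludes none.

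The only itemised list of intraoperative data is Table 3, in the same section. Its intraoperative column includes gases at T1 to T4 ("Blood gas analysis: pH/ PaCO_2_/ PaO_2_/ Hb/ Lac/ Glu"), hypotension, bradycardia, transfusion, blood loss, vasoactive drugs, opioids and durations.

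The arms are defined by some of these quantities. Under Study design, setting and participants, the intervention arm has "PaCO_2_ 45 ~ 55 mmHg, pH > . 7.2" and the control arm "PaCO_2_ 35 ~ 45 mmHg". Under Anesthesia maintenance, after intubation "PaCO_2_ will be maintained within the respective target values in both groups".

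**The concern.** Randomisation makes the arms comparable on what precedes it. A variable measured afterwards may be a consequence of allocation, and holding it fixed can remove part of the effect under study. PaCO2 is the extreme case here, because the arms are defined by their PaCO2 targets. Comparing the arms at equal PaCO2 asks what the ventilation strategy does other than through PaCO2, which is not the trial's question. Adjustment for a post-randomisation variable can also create an association through unmeasured causes that it shares with rSO2.

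Readers often take an adjusted estimate as the more credible one. A real benefit could therefore be reported as disappearing after adjustment. The plan does not prevent this, since no sentence ranks the adjusted estimate against the unadjusted one.

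**Working it through.** **The plan's own figure.** Sample size calculations gives a difference of 8 points (0 against 8), two-sided 5% significance, 90% power, an unpaired t-test and a total of 68. No SD is stated. The t-test returns 68 for an SD of about 9.9 to 10.0, so SD 10 is used below. The allowance for loss reproduces: 68 / (1 − 0.10) = 75.6, rounded up to 76.

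**Assumptions not in the documents.**
- The arms differ by 10 mmHg in mean PaCO2. This is the gap between the midpoints of the two target ranges, 50 and 40.
- The within-arm SD of PaCO2 is 3 mmHg, varied from 2 to 5 for the variance inflation.
- The outcome SD is 10, with 34 evaluable patients per arm.
- A share s of the 8-point effect runs through PaCO2, with s from 0 to 100%.

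**Bias.** With one intraoperative PaCO2 value in the model, the arm coefficient estimates only the part of the effect that does not pass through PaCO2, (1 − s) × 8. For s = 25%, 50%, 75% and 100% that is 6, 4, 2 and 0.

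**Precision.** The unadjusted SE is 10 × √(2/34) = 2.43. PaCO2 nearly separates the arms, so adding it inflates the variance of the arm coefficient by 1 + gap² / (4 × SD²):
- SD 3: 1 + 100/36 = 3.8
- SD 5: 1 + 100/100 = 2.0
- SD 2: 1 + 100/16 = 7.3

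At SD 3 the SE becomes 2.43 × √3.78 = 4.7.

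**Simulation, 4,000 trials per row:**

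| Share through PaCO2 | Unadjusted estimate | Unadjusted power | Adjusted estimate | Adjusted SE | Adjusted power |
|---|---|---|---|---|---|
| 0% | 8.0 | 90% | 8.0 | 4.8 | 38% |
| 25% | 8.0 | 90% | 5.9 | 4.8 | 24% |
| 50% | 8.0 | 89% | 3.9 | 4.8 | 13% |
| 75% | 8.0 | 90% | 2.0 | 4.7 | 7% |
| 100% | 8.0 | 90% | −0.1 | 4.7 | 5% |

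The last row is the 5% expected when no effect remains.

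**Is the direction certain?** No. With a 50% share and an unmeasured common cause of PaCO2 and rSO2, the adjusted estimate averaged about 1.1 for a weak common cause (loading 0.3 on each) and −7.9 for a stronger one (loading 0.6). With a mediator acting against the total effect it rose to 11.9.

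**The case against.** Several points on the other side are sound.

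- **Covariates not named.** A reader might infer that PaCO2 and pH are definitely in the model. The text does not say so. Table 3 is cited for the between-group tests, not for the regression, and a covariate list is something an article may leave to the analysis plan. What stands is that the article positively admits intraoperative data as a class, and that PaCO2 and pH belong to that class in its own table.
- **The Discussion.** It says "Throughout the procedure, we can control for potential confounders such as PaCO_2_, pH, MAP, and intraoperative body position". A reader might take this as a plan to adjust statistically for PaCO2. It reads more naturally as clinical control during the operation: MAP and position are not Table 3 items, and the next sentence plans adjustment for preoperative MAP, Hb and cardiac output only. Calling PaCO2 a confounder is loose wording, but it does not show that PaCO2 enters a model.
- **Full collapse to zero.** This needs the whole effect to run through PaCO2. The arms also differ in tidal volume and respiratory rate, so complete mediation is not given.
- **Overfitting.** Entering every Table 3 item at every time point would use about 58 covariate parameters. Nothing in the document says that they would all be entered together, so this count is no evidence against the plan.
- **Primary analysis.** A reader might infer that the plan has no valid primary analysis. That goes too far. The unadjusted regression on group is equivalent to the unpaired t-test on which the trial was sized, it is listed first, and it falls under intention to treat. What is missing is a sentence ranking it above the adjusted estimate.

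**Conclusion.** The point holds for the adjusted estimate. As written, the plan allows post-randomisation variables, including the randomised exposure, into a model whose output is called an adjusted effect size for the primary outcome. If they are entered, that effect size and its interval do not estimate the effect of allocation. They are biased for the total effect, most likely towards zero under the protocol's own hypothesis, though not with certainty.

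Under the stated assumptions, the loss from adding one PaCO2 value is proportional to the share of the effect that PaCO2 carries. The SE roughly doubles, from about 2.4 to 4.7, whatever that share is. The variance inflation is 3.8, with a range of 2.0 to 7.3 for a within-arm SD of 5 down to 2 mmHg.

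The documents do not support the stronger conclusion that the trial's primary result is invalid or must shrink to nothing. The unadjusted intention-to-treat comparison is planned, powered and untouched. The defect is confined to the adjusted estimate and to the lack of any statement of which estimate decides.

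**What to change.** In Statistical analysis, replace the sentence on the adjusted model with four statements:

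1. The primary estimate is the unadjusted intention-to-treat difference between arms in the T0-to-T4 change in rSO2, with its 95% confidence interval. The same model with T0 rSO2 as a covariate is an acceptable alternative. It is an optional gain in precision, not a needed correction, and one of the two should be named in advance.
2. The adjusted model is supportive and contains only a short named list of pre-randomisation variables already collected, for example T0 rSO2, age and baseline Hb.
3. Intraoperative variables, including the blood gases, are described by arm.
4. Any model containing intraoperative PaCO2, pH or another post-randomisation variable is labelled exploratory mediation and is not reported as an effect of allocation.

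In the Discussion, say that PaCO2 and pH are controlled clinically as part of the allocated strategy, and do not call them confounders.

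The cost is wording only. No new data are needed and the sample size of 76 does not change.
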